### Participants and recruitment

Participants will be employees reporting high levels of work-related fatigue. Every employee – regardless job position – can sign up for participation. Participants will be recruited through advertisements with study information in personnel magazines, on facebook pages, and on intranet of large organizations in the region(s) in which the intervention will be carried out. Furthermore, advertisements and news items will be placed in (local) newspapers and on social media.

Inclusion criteria will be based on existing cut-off scores on two validated measures of work-related fatigue: a) ≥2.2 on the emotional exhaustion scale of the Dutch version of the Maslach Burnout Inventory [49]; b) ≥22 on the Fatigue Assessment Scale [50]. Participants can fill out these two scales on the study website (www.runtervention.nl). When participants score high on both scales, the researcher ([name]) will ask these participants for further information about exclusion criteria by email. Exclusion criteria will be: a) ≥ one hour exercising a week; b) fatigue attributable to a medical condition; c) currently or in the past six months receiving psychological and/or pharmacological treatment; d) drug dependence; e) contraindications to exercise. Contraindications to exercise will be measured by the Physical Activity Readiness Questionnaire (PAR-Q; [51]). Eligible participants will be invited for an appointment with the first author ([name]) or research assistants. During this appointment, the baseline measures (T0; except for the two measures of work-related fatigue that are already filled out) will be completed, the cognitive performance tests will be done, and the randomization procedure will be carried out. A separate appointment will be planned for the aerobic fitness test.

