### Randomization and blinding

Participants will be randomly assigned to either an exercise condition or a wait list condition at a 1:1 ratio. Because the intention is to conduct the exercise intervention in groups of 10 participants, randomization will be based on a block size of 20. When the number of 20 eligible participants in a block is reached, participants in the exercise intervention condition start the intervention and the participants in the wait list condition remain on the wait list. The randomization procedure will be carried out after the participant has completed the baseline measurement (T0). The randomization procedure will be executed by the first author ([name]) or research assistant, using sealed opaque envelopes. The participant opens the envelope and tells the researcher to which condition (s)he has been assigned.

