#### Aerobic fitness

We will measure aerobic fitness using the estimated maximal oxygen uptake (VO_2max_), obtained from the UKK walk test [75]. This test has found to be valid and feasible for a healthy adult population [75]. During this test, participants have to walk 2 km as fast as possible. The test will take place on a 400 m outdoor track in groups of (maximum) ten participants. Participants start individually every 30s. The instruction is as follows: “Walk the distance as fast as you can, but do not risk your health”. Immediately after the walk, the heart rate and walking time will be measured. The variables used to calculate VO_2max_ are walking time, heart rate, body weight, height, and gender (see [75] for exact equations).

We will also measure participants’ *subjective costs* of doing the UKK walk test. The questions used for this purpose are similar to those asked before and after the cognitive tasks, except that we add another question about how ‘short of breath’ participants are immediately after the test. Completion of the test, including filling out the items about subjective costs, takes about 25 min.

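### The baseline walk test is not fixed before the envelope is opened, so T0 aerobic fitness may be measured after participants know their arm

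*Protocol article*

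**What the plan says.** Under Participants and recruitment, eligible people are invited to an appointment. There, "During this appointment, the baseline measures (T0; except for the two measures of work-related fatigue that are already filled out) will be completed", and at the same visit "the cognitive performance tests will be done, and the randomization procedure will be carried out". The next sentence takes one T0 measure out of that visit: "A separate appointment will be planned for the aerobic fitness test".

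Under Randomization and blinding, the rule on order is: "The randomization procedure will be carried out after the participant has completed the baseline measurement (T0". Allocation is not concealed from the participant after that: "The participant opens the envelope and tells the researcher to which condition (s)he has been assigned". The start waits for the block to fill: "When the number of 20 eligible participants in a block is reached, participants in the exercise intervention condition start the intervention".

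Table 1 lists VO2max and the subjective costs of the walk test at T0 and T6. The Aerobic fitness section describes a 2 km walk on an outdoor track, held "in groups of (maximum) ten participants", with the instruction "Walk the distance as fast as you can, but do not risk your health". VO2max is then estimated from walking time and heart rate, together with weight, height and gender. Under Analyses of primary and secondary outcomes, aerobic fitness is tested by the condition-by-time interaction from T0 to T6.

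**The concern.** One section requires all of T0 to be finished before allocation. Another opens the envelope at a visit that does not include the walk test, and does not say that the walk test has already taken place. Staff who follow the recruitment section in the order it is written would take the T0 walk test after allocation is known.

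That matters for this measure because the result depends on how hard the participant chooses to walk. Someone told that they will start running soon and someone told that they must wait may differ in effort, in activity before the test, or in whether they attend at all. A baseline taken before allocation can differ between arms only by chance. One taken afterwards can also differ because of the allocation. The planned test uses the change from T0 to T6, so such a difference would be read as an effect of the intervention, in either direction.

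The limitations section plays down the lack of blinding on the ground that the outcomes need no judgement by assessors. That argument does not cover the participant's own effort.

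**Working it through.** **Order of events.** The plan gives no figure on this point, so the first step is to set the statements side by side.

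| Source | Statement | Consequence |
|---|---|---|
| Participants and recruitment | T0 questionnaires, cognitive tests and randomisation share one appointment | The arm is known at the end of that visit |
| Participants and recruitment | The walk test has its own appointment | Its position relative to randomisation is not stated |
| Table 1 | VO2max and the test's subjective costs belong to T0 | T0 is incomplete without the walk test |
| Randomization and blinding | Randomisation follows completion of T0 | The walk test should come first |

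All four statements hold only if the walk test precedes the randomising appointment. Nothing says that it does. People screened online and by e-mail are invited to the randomising appointment, and the walk test is mentioned last, so the natural reading is that it comes afterwards. The flow diagram (Fig. 1) is not available in the text reviewed and may settle the order.

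**How a T0 shift enters the estimate.** The contrast is (T6 − T0) in the exercise arm minus (T6 − T0) in the wait-list arm. If knowing the arm lowers the exercise arm's estimated T0 VO2max by b SD and changes nothing at T6, the contrast moves by +b. A rise moves it by −b.

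**Illustrative size.** Inputs:
- N = 90 in total, from the Sample size section, taken as stated.
- Two-sided 5 % level, from the same section.
- b = 0.1 to 0.3 SD, assumed.
- Pre-post correlation r = 0.5 to 0.8 for VO2max, assumed.
- No true effect on fitness.

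The change score has variance 2(1 − r) in SD² units. With N/2 per arm, the between-arm contrast has variance 2(1 − r) × 4/N. The noncentrality of the F test (1 and N − 2 degrees of freedom) is therefore λ = b² × (N/4) / [2(1 − r)].

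For b = 0.2 and r = 0.5: λ = 0.04 × 22.5 / 1.0 = 0.90. For b = 0.2 and r = 0.8: λ = 0.04 × 22.5 / 0.4 = 2.25.

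| b (SD) | Rejection, r = 0.5 | r = 0.7 | r = 0.8 |
|---|---|---|---|
| 0.1 | 7.6 % | 9.3 % | 11.5 % |
| 0.2 | 15.5 % | 22.8 % | 31.7 % |
| 0.3 | 29.1 % | 44.3 % | 60.5 % |

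The nominal rate is 5 %. The table shows how sensitive the test is to such a shift. It is not evidence that a shift would occur.

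**Side point on the block.** Envelopes are opened one participant at a time in fixed blocks of 20. Someone who tracked every earlier result and always guessed the arm with more places left would be right on 10 + 2^19/C(20,10) − 0.5 = 10 + 524,288/184,756 − 0.5 = 12.34 of 20, against 10 by chance. On average 20/11 = 1.82 allocations at the end of a block would be certain in advance.

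**The case against.** **The order is not stated.** A reader might infer that the plan measures T0 fitness after allocation and so breaks its own rule. The text does not establish this. A walk test held before the randomising visit would satisfy every statement, and Fig. 1 may show that order. Testing in groups of up to ten is track logistics and says nothing about timing. This objection stands: what can be shown is an order left open and two sections that appear to conflict.

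**The effect may be small or cancel.** The T6 walk test is unblinded and effort-dependent whatever is done at T0, and an effort difference of the same size at both times drops out of the change. This also stands, so the calculation applies only to a difference specific to T0. In addition, b is a shift in estimated VO2max, not in walking speed. Heart rate enters the estimate as well and the article does not reproduce the equations, so a given change in effort cannot be converted into b from the documents.

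**Wider consequences do not follow.** A reader might also infer that staff could steer enrolment by predicting the last allocations in a block. The arithmetic is right, but the gain is about 2.3 guesses per 20. Eligibility is settled before the visit by cut-off scores, e-mailed questions and the PAR-Q, and the envelopes are sealed and opaque. No route to selective enrolment is shown. Likewise, a variable wait between T0 and the start adds noise to the first interval of the weekly growth models, but no bias between arms is shown.

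What remains is that the order of a T0 outcome and its allocation is left unprotected, and that following the recruitment section as written can bias a planned test.

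**Conclusion.** The point holds in a limited form. The recruitment section opens allocation at a visit that excludes the T0 walk test and nowhere fixes that test beforehand. This appears to conflict with the requirement that T0 be complete before randomisation.

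If the walk test comes second, any arm difference specific to T0, in effort or in attendance, can distort the comparison for VO2max (Hypothesis 2g) and for the test's subjective-cost items. Allocation itself stays random; only the measurement is exposed. The primary outcome is not affected by this point.

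The size is unknown. The rejection rates of about 8 % to 61 % rest on an assumed shift of 0.1 to 0.3 SD, an assumed pre-post correlation of 0.5 to 0.8, 90 participants, no true effect and no matching shift at T6. Because the remedy is simple and protects a named hypothesis, the change should be made, but it concerns one secondary outcome.

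**What to change.** Reconcile the two sections by stating that the T0 walk test takes place before the envelope is opened, so that allocation is revealed only after every T0 measure is complete.

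Preferably, open the envelopes for a block together once its 20 participants have completed T0, shortly before the intervention starts. This also shortens the time that participants know their arm before the start, and stops staff inferring the last allocations in a block.

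No new assessment is needed. The cost is that participants learn their arm later than at the first appointment. Under the preferred version they may have to wait for the block to fill, and the envelope step has to move out of the individual appointment.

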### Randomization and blinding

Participants will be randomly assigned to either an exercise condition or a wait list condition at a 1:1 ratio. Because the intention is to conduct the exercise intervention in groups of 10 participants, randomization will be based on a block size of 20. When the number of 20 eligible participants in a block is reached, participants in the exercise intervention condition start the intervention and the participants in the wait list condition remain on the wait list. The randomization procedure will be carried out after the participant has completed the baseline measurement (T0). The randomization procedure will be executed by the first author ([name]) or research assistant, using sealed opaque envelopes. The participant opens the envelope and tells the researcher to which condition (s)he has been assigned.

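### A fixed block of 20, disclosed one person at a time to the team that also screens, leaves late allocations in each block predictable; allocating each closed block at once would remove this

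*Protocol article*

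**What the plan says.** All of this is in the protocol article.

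- **Ratio and block (Randomization and blinding).** Allocation is 1:1 and "randomization will be based on a block size of 20". The size follows from logistics: "Because the intention is to conduct the exercise intervention in groups of 10 participants". The end of a block is visible to everyone involved: "When the number of 20 eligible participants in a block is reached, participants in the exercise intervention condition start the intervention".
- **Disclosure (same section).** The first author "or research assistant, using sealed opaque envelopes" carries out the procedure after the baseline measurement. Then: "The participant opens the envelope and tells the researcher to which condition (s)he has been assigned".
- **Screening and appointments (Participants and recruitment).** Applicants complete the two fatigue scales online. For those above both cut-offs, the researcher "will ask these participants for further information about exclusion criteria by email". The next step is an individual visit: "Eligible participants will be invited for an appointment with the first author" or research assistants. Baseline questionnaires, cognitive tests and randomisation all take place at that visit. The aerobic fitness test has its own appointment, whose timing relative to randomisation is not given.
- **Blinding (Strengths and limitations).** Participants, trainers and researchers all know the condition. The same section lists the reduction of selection bias among the benefits of the design.

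The protections stated are the sealed opaque envelopes and randomisation after T0.

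**The concern.** An opaque envelope conceals one allocation. It does not conceal the number of places left in each arm when the block size is fixed and known and every earlier result in the block has been announced. As a block fills, the next allocation becomes easier to guess, and once one arm has its 10 the rest are certain.

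What is at stake is allocation concealment at entry. If someone who decides a borderline exclusion, or who goes first into an appointment slot, can anticipate the arm, the two groups may differ at entry in ways that randomisation was meant to prevent. Randomising after T0 stops a person's own allocation from colouring the measures taken at that visit. It does not stop the results of the preceding participants from influencing who comes next.

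**Working it through.** The plan gives no figure for predictability, so there is none to reproduce. The check asks how much a person who knows the tally could predict.

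**Inputs.** Ratio 1:1 and block size 20, so m = 10 per arm (Randomization and blinding). Planned recruitment 108 (Sample size), which is 5 × 20 + 8.

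**Assumption.** The observer knows the exact tally at the moment of the decision and always guesses the arm with more places left.

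**Step 1: allocations that are certain.** The expected number per block is 2m/(m + 1) = 20/11 = 1.82, or 9.1% of 20. The chance that at least the last k allocations are certain is 2·C(20 − k, 10)/C(20, 10):

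| k | Probability |
|---|---|
| 1 | 100% |
| 2 | 47.4% |
| 3 | 21.1% |
| 4 | 8.7% |

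**Step 2: correct guesses.** The expected number per block is m + (4^m/C(2m, m) − 1)/2. With m = 10, 4^10 = 1,048,576 and C(20, 10) = 184,756, so the ratio is 5.675 and the result is 10 + 4.675/2 = 12.34 of 20, or 61.7%. An exact recursion over the remaining places gives the same two expected values. By position in the block, the chance of a correct guess is:

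| Position | Chance correct |
|---|---|
| 1 | 50% |
| 10 | 59% |
| 16 | 67% |
| 18–19 | 74% |
| 20 | 100% |

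**Step 3: the whole trial.** Five full blocks give 5 × 1.82 = 9.1 certain allocations. The first 8 places of a sixth 10 + 10 block add none, because neither arm can be full after 8. The total is therefore about 9. Correct guesses come to about 66 of 108 (61%): 5 × 12.34 = 61.7 from the full blocks and about 4.3 from the last 8.

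**Step 4: comparison with smaller blocks.** A fixed block of 4 would give 70.8% correct guesses and 33% certain allocations. A block of 20 therefore leaks less than a small one, and shrinking the block would make matters worse.

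**The case against.** The case for leaving the procedure alone has substance.

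- **Who does what.** The article shows one research team screening, holding appointments and allocating. It does not show one individual doing all three, it does not say who books appointments, and it does not say that anyone keeps a tally. These are inferences. This stands.
- **Little room for discretion.** The fatigue cut-offs are self-completed online before contact, and several exclusions are rule-based (weekly exercise, recent treatment, the readiness questionnaire). What remains is the non-scored exclusions, such as whether fatigue has a medical cause, and the order of appointments. This stands.
- **Timing.** Exclusions are checked by email before the appointment, and others may be randomised in between. The 62% is therefore an upper bound for that step. This stands.
- **Mitigation.** The main analysis tests change from T0, and wait-list participants receive the intervention after six weeks, which lessens any motive to favour an arm. Both soften the consequence, but neither restores concealment.
- **Open label and self-report.** Bias from unblinded self-reporting would remain under perfect concealment and should not be added to this point. This stands.

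A reader might also infer that the article contradicts itself on selection bias. It does not: Strengths and limitations claims that such bias is reduced, not that it is absent, and a randomised trial with some guessable allocations still reduces it.

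None of this removes the core point. The fixed block, the sequential disclosure and the shared team are stated in the article, and opaque envelopes do not hide the remaining balance.

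**Conclusion.** The concern holds as a modest weakness in concealment that is worth correcting. For someone who tracks the tally, about 1.8 of every 20 allocations are certain, about 9 over the five full blocks, and at most about 62% can be guessed. These figures measure predictability, not bias; no effect on the fatigue outcome has been estimated.

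The conclusion rests on three assumptions: blocks are balanced 10 + 10, someone involved in screening or scheduling can learn the running count, and some entry or booking decisions are made after earlier results in the block are known. It would be tempting to read the article as showing that entry will be steered, or that one person controls the whole chain. It shows neither. The supportable statement is that the procedure leaves an opening, limited to non-scored exclusions and appointment order, and that this weakens the reduction in selection bias on which the article's causal claim partly depends.

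**What to change.** Use the waiting period that the design already has. Since no group starts until 20 eligible people are in the block:

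1. Confirm eligibility and complete every T0 measure for all 20, including the separately scheduled fitness test, so that no baseline is taken with the arm already known.
2. Close the list and fix the participant order.
3. Allocate all 20 at once, 10 per arm, and inform participants.
4. Treat the final partial block (108 = 5 × 20 + 8) as one closed batch, split 1:1 into 4 + 4.

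No eligibility or booking decision within a batch then follows a known allocation in that batch. This needs no additional staff: it works whoever draws the sequence, provided that the draw comes after the list is closed. For the full blocks, group size and start rule stay as planned.

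The cost is small. Participants learn their arm only when the block closes, not at the appointment. Some may withdraw before allocation and need replacing, and the fitness tests must be scheduled before the list closes.

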### Conditions

#### Exercise intervention condition

The exercise intervention will take six consecutive weeks and comprises of low intensity running, meaning that participants should be able to talk while running [52]. This intensity is chosen, because research has indicated that a low intensity is effective in reducing fatigue [48] and to reduce the risk of injuries [53]. Furthermore, the prospect of high intensity exercise may hamper participants’ motivation to engage in or maintain exercise [54], especially when participants are already fatigued. In total, participants will run three times a week (18 running sessions in total): twice a week in a group of ten people guided by a running trainer, and once a week independently. Each running session lasts one hour, and consists of 15 min warming up, 30 min running alternated with walking, and 15 min cooling down. During the intervention, a fixed running schedule will be used in which the periods of running gradually increase, and the periods of walking gradually decrease. The goal is to achieve a 20 min period of continuous running in the last session. Each week, participants receive the running schedule of the upcoming week by email, as to know the content of the running sessions of that week beforehand. If participants miss a guided running session, they can catch up by doing an additional independent session in the same week that the guided session was originally planned. Participants will be advised to keep at least one rest day (i.e. no running session) in between the running sessions to reduce the risk of injuries [55].

Trainers of the exercise intervention will be experienced running trainers, additionally trained in the principles of ‘running therapy’, the most commonly applied form of exercise therapy for mental health problems in the Netherlands [56, 57]. Trainers will be instructed to watch participants’ level of exertion during the running sessions and to urge participants to lower their speed if they are short of breath and not able to talk. Further, they will be instructed to ensure that the focus during the running sessions is not on ‘performance’ but rather on ‘pleasure’.

### Wait list condition

During the six-week exercise intervention condition, the participants in the wait list condition receive no intervention. After these six weeks, participants will receive the exercise intervention as well.

